### Sample size

Sample size for the pilot trial is calculated to recruit at least 30 participants in each arm in order to estimate the pooled standard deviation of the outcome with a reasonable degree of precision for the full trial [48, 49]. We have estimated that attrition will be 20% based on a preliminary feasibility-controlled case series [50] and that a further 20% joining the STAR cohort will either not meet the first trial inclusion criteria or not accept the offer of treatment.

Sample size for the full trial will be based upon results obtained in the pilot. The calculation will be based upon the obtained effect size (SMD) for the primary outcome, significance (alpha error) of 0.05 and power of 80% and adjusted according to the levels of attrition observed. If an effect size of .4 is obtained in the pilot, then the outcomes of approximately 100 participants per group will be required. If estimated attrition of 40% is correct, then 166 participants per group will need to be recruited to the cohort.

Participants are recruited from registered charities, schools, word of mouth and support groups. The majority of participants are recruited from the city of Sheffield; however, participants are also recruited nationally and the feasibility of on-line treatments assessed.

### Inclusion/exclusion criteria

Inclusion criteria for the STAR cohort are children aged 5–18 (inclusive) with a carer-reported diagnosis of ADHD (date, venue and diagnosing physician) and a carer-reported Conners Global Index (CGI) *T* score of at least 55 (denoting mild atypicality (Table 1). Inclusion criteria for the trial are a carer-reported CGI score of at least 65 (indicating a significant problem) (Table 1).

**Table 1 Tab1:** Interpretive guideline for Conners’ *T* scores and percentiles

*T* score	Percentile	Guideline
70+	98+	Markedly atypical (significant problem)
66–70	95–98	Moderately atypical (significant problem)
61–65	86–94	Mildly atypical (possible problem)
56–60	74–85	Slightly atypical (borderline)
< 30–55	< 2–73	Average (typical: should not raise concern)

Exclusion criteria to both cohort and trial are children below the age of 5 or adults over 18; children with terminal, severe, life-limiting conditions; and families where English is not written or spoken (as the project does not have funds to provide a translation service). Exclusion criteria to the trial are children currently receiving treatment by a homoeopath or a nutritional therapist and children with CGI *T* scores below 65.

### Outcome measurement

Carers of children with ADHD are asked to complete carer questionnaires (CQs) sent to them by post or completed on-line (www.starsheffield.com).The CQ includes the 10-item Conners’ Global Index (CGI) [47]; the 18-item Swanson, Nolan and Pelham Teacher and Parent Rating Scale (SNAP) [51]; the 9-item Child Health Utility health-related quality of life (CHU-9) measure [52]; and questions about resource use. The last page asks for consent from carers and children to be contacted again, for their school to be contacted, personal and school contact details.

Where consent is given, schools are sent a teacher’s questionnaire (TQ) and an information letter. They are not informed about treatment allocation. The TQ includes the CGI, SNAP, and questions about school-specific resource use, attendance, disruption and exclusion. Schools which do not want to participate are not contacted again.

Control group participants are not informed that they have not been selected for a treatment but continue to be sent questionnaires at the same time intervals as treatment groups. CQs and TQs are sent out every 6 months to all cohort participants. Those refusing the offer of treatment are still asked to complete outcome measures as usual every 6 months and considered members of the offer group.

### The interventions

Homoeopaths are registered with one of the four main bodies representing homoeopaths in the UK. Nutritional therapists are registered with the British Association of Applied Nutrition and Nutritional Therapy and are members of the Complementary and Natural Healthcare Council. All therapists are CRB checked, complete an on-line NSPCC child protection course (https://www.nspcc.org.uk/what-you-can-do/get-expert-training), attend a 1-day training course on risk and receive guidelines in management of ADHD and serious adverse events.

Both interventions are offered to participants for a maximum of 1 year consisting of a maximum of eight appointments. Consultations take place at Complementary Medicine Centres, participant’s homes or on-line. First consultations last for up to 1½ h and follow-ups last up to 40 min approximately every 6 weeks for up to 1 year resulting in a total of up to seven contact hours. Homoeopaths conduct fact-finding consultations on the basis of which they prescribe homoeopathic medicines, guided by underlying basic homoeopathic principles [53]. Treating ‘like with like’ is the core principle: that substances causing certain symptoms in healthy persons may cure those same symptoms in those who are ill. Nutritional therapists take an initial health history and discuss and agree with participants an appropriate range of options such as elimination diets, healthy food and menu options, reducing aggravators such as food colourings or sugar; improving fluids intake, lifestyle issues such as sleep; specific dietary intervention for symptoms; and supplementation.

At each consultation, therapists ask participants and/or their carer (dependent on age) to complete Measure Your Own Medical Outcome Profile (MYMOP) [54]. This patient generated outcome measure consists of 4 self-chosen items measured using a Likert-type scale of 0 (as good as it could be) to 6 (as bad as it could be): two symptoms considered most bothersome, an activity ADHD limits participation in, and well-being. Diminution of scores represents improvement. This personalised measure allows participants to select their key concerns and document how they change over time. It is a validated outcome measure considered appropriate to capture non-specific effects.

Therapists also ask about any adverse events experienced by participants which are recorded according to the Common Terminology Criteria for Adverse Events guidelines [55]. Therapists are instructed to report adverse events of level 3 or more to the PI within 24 h, who refers them immediately to the study Data Management and Ethics Committee for appropriate action.

Information regarding adverse events for children with ADHD in response to homoeopathic treatment suggests that there may be occasional mild transient increases in symptoms, which are however usually associated with overall feelings of well-being. Information in response to nutritional therapy suggests that there may be occasional minor side effects from supplementation.

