Acceptability of TQ and CQ	Number of TQs and CQs completed at baseline and 6 months; number of email/telephone/ paper responses	Adjustment of measure, collection methods and trial parameters. Questions reworded or removed dependent on discussion with carers and teachers, and optimum means of delivering questionnaires explored
Adverse events	Clinicians records	No severe adverse events as defined by the Common Terminology Criteria for Adverse Events guidelines
Appropriate outcome measurement	Number of missing items	Adjustment of measure
Recruitment of therapists	Number recruited fulfilling criteria	At least two for each therapy
Statistical analysis	ANCOVA	Meets assumptions

Whether suitable homoeopaths and nutritional therapists can be recruited will be assessed, with recruitment of two therapists for each intervention considered the minimum required. The uptake of treatment will measure the number of appointments kept and missed; the taking of homoeopathic medicines; and the implementation of advice, diets, and the taking of supplements. At least 30% will need to have accessed treatment, and at least 70% of those to have attended at least three consultations, to continue to the full trial. It is anticipated that there may be high dropout rate and chaotic uptake. The percentage of participants refusing treatment will be considered to determine acceptable levels of refusal since too many refusers may lead to high chance of a type II error and inadequate information to estimate critical parameters for a full trial with reasonable precision.

Adverse events will be documented to measure the safety of the interventions using the Common Terminology Criteria for Adverse Events (CTCAE, 2010). Any severe adverse events as a result of treatment will mean the intervention will not continue to full trial.

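### The zero-event safety criterion rests on therapists' records alone, so it is easier to pass the more children start treatment and then stop attending.

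*Protocol article*

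**What the plan says.** The interventions section makes the treating therapists the enquirers: "Therapists also ask about any adverse events experienced by participants", with the events recorded by CTCAE. This follows directly on the procedures done at each consultation. Urgent reporting takes the same route: "Therapists are instructed to report adverse events of level 3 or more to the PI within 24 h", and the PI refers the event to the study committee. No route from carer or school is described.

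Table 2 gives the measurement for the adverse-event criterion as "Clinicians records" and the condition for continuing as "No severe adverse events as defined by the Common Terminology Criteria for Adverse Events guidelines". The text below the table words it differently: "Any severe adverse events as a result of treatment will mean the intervention will not continue to full trial".

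The Outcome measurement section lists the carer questionnaire as two symptom scales, "the 9-item Child Health Utility health-related quality of life (CHU-9) measure [52]; and questions about resource use". The teacher questionnaire covers symptoms, school resource use, attendance, disruption and exclusion. Neither list has an adverse-event item. Both questionnaires go every 6 months to the whole cohort, including refusers and the treatment-as-usual (TAU) arm. Patient-centred outcomes adds hospital and GP attendances, collected as resource use and not linked to the safety criterion.

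On attendance, the Feasibility outcomes section states: "It is anticipated that there may be high dropout rate and chaotic uptake". To continue, at least 30% must access treatment and at least 70% of those must attend three or more consultations.

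**The concern.** Safety of the interventions is a stated stage 1 objective, and the adverse-event criterion can end an intervention's progress to the full trial. A criterion of zero events depends on who is observed and for how long, because an event that nobody asks about counts as no event. Observation here depends on attendance. A child who stops because of an adverse event is the child the criterion most needs to see and is least likely to see. The protocol expects many children to stop, so the criterion is weakest under the conditions it foresees.

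A second, smaller problem is that Table 2 requires no severe events at all, while the text counts only those resulting from treatment. The same event could fail the criterion under one wording and pass under the other.

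**Working it through.** The protocol gives no figure for adverse-event coverage and no event rate, so there is nothing of its own to reproduce here. Its sample-size figures are not affected.

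**Inputs from the protocol article**
- Pilot size: at least 30 per arm (Sample size).
- Uptake floor: 30% access treatment; 70% of those attend at least three consultations (Feasibility outcomes).
- Visits: up to eight, about 6 weeks apart, within 1 year (The interventions).

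**Assumptions**
- Each visit covers the time since the previous one, so coverage runs from first to last visit.
- Severe-event rate r of 1-5% per child-year, constant over time and independent between children. This range is illustrative.

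**Step 1: starters at the floor.** 0.30 × 30 = 9 children.

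**Step 2: share of starter time covered.** A third visit falls at about week 2 × 6 = 12. If all 9 starters attend exactly three visits, coverage is 9 × 12 = 108 of 9 × 52 = 468 child-weeks, or 23%. This share is 12/52 per child and does not depend on how many start. The true floor is lower: only 0.70 × 9 = 6.3 starters need three visits. If the rest attend once, coverage is 6.3 × 12 = 75.6 of 468, or 16%.

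**Step 3: the other end.** A child attending all eight visits 6 weeks apart is last seen at about week 7 × 6 = 42. That covers 42/52 = 81% and leaves about 10 weeks. Wider spacing would shorten this gap.

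**Step 4: chance that an event occurs among the 9 starters in the year.** 1 − (1 − r)^9
- r = 1%: 1 − 0.99^9 = 0.086
- r = 5%: 1 − 0.95^9 = 0.370

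**Step 5: chance that an event falls in the covered weeks.** Covered time is 108/52 = 2.08 child-years, so 1 − (1 − r)^2.08
- r = 1%: 0.021
- r = 5%: 0.101

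**Step 6: effect on a zero-event criterion.** At r = 5%, the chance of seeing no event is 1 − 0.370 = 63% with the full year covered and 1 − 0.101 = 90% with three visits each. At r = 1% it is 91% and 98%. Less observation raises the pass probability although the risk is unchanged.

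**The case against.** **The article is condensed.** Its questionnaire list is not exhaustive: diagnosis details are collected but not named in it. Follow-up of withdrawn children may stand in a fuller protocol. This stands as a limit, because that therapists are the only source is an inference. But the article does more than stay silent: it names the data source for this criterion and describes no other route.

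**The floor is a worst case.** The protocol assumes 20% attrition and a further 20% ineligible or refusing, which suggests more than 9 starters. That would raise the probabilities in steps 4 and 5, but not the 23%, which depends only on visits attended.

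**Stronger readings do not hold.** A reader might infer that an intervention could be stopped on a background event for want of a TAU rate. Only the Table 2 wording allows that; the text rule requires the event to result from treatment, and a zero-event rule does not formally need a comparator. A reader might also put the 108 child-weeks over all 30 offered children, 108/(30 × 52) = 7%. That denominator includes 21 children who never started and cannot have a treatment-caused event. Nor is the chance of an event among 30 children over a year, 1 − (1 − r)^30 = 26-79%, the chance that the rule is triggered, since an unrecorded event triggers nothing.

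**The remedy is limited.** Thirty TAU children would give 30 × 0.01 = 0.3 to 30 × 0.05 = 1.5 expected events, too few for a usable rate. Children who stop attending may not return questionnaires either; Table 2 accepts a 30% return at 6 months. Both points stand, and they confine TAU data to descriptive context.

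**Conclusion.** The concern holds for children who start treatment and then stop attending. As written, the criterion is judged on records whose completeness falls with attendance, and it becomes easier to pass as attendance falls. At the plan's floor about 23% of starter time is covered. At an assumed 1-5% per child-year, an event occurs among the 9 starters in about 9-37% of pilots but falls in the covered weeks in only about 2-10%. These probabilities rest on the assumed rate and on three visits per starter; the direction of the effect depends on neither.

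The documents do not support the wider conclusion that the safety objective fails for want of a TAU comparator, or that refusers form a material part of the gap. The conflict over attribution between Table 2 and the text is a separate defect that needs reconciling. The point should be acted on because it bears on a continuation decision and a stated objective. It does not touch the primary outcome.

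**What to change.** Add one neutral item to the six-monthly carer questionnaire, for all three arms, asking about adverse or serious health events since the last questionnaire. Grade the answers on the same CTCAE scale and send level 3 or higher reports to the same committee. Name this source beside therapists' records in the Table 2 row. When the criterion is judged, tabulate these reports and the hospital and GP attendances already collected by randomised arm, next to the therapist records, with TAU data as descriptive context only. Reconcile the Table 2 and text wordings on attribution.

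The cost is one questionnaire item and one table, with no extra staff or visits. Six-month carer recall is coarser than a consultation record, non-return will leave gaps, and carers bear a small added burden. The item supplements therapist records and does not replace them.

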### Outcomes

#### Patient-centred outcomes

The primary outcome measured is ADHD symptomatology measured using CGI, consisting of a 10-item total score and two sub-scores measuring restlessness/impulsivity (7 items) and emotional lability (3 items). The outcome is reported by carers (unblinded) and teachers (blinded), and each intervention is compared to usual care. Secondary outcomes are carer proxy health-related quality of life (CHU-9) and sleep. Resource use is collected by asking about medication use; further ADHD interventions being used; hospital, GP, social worker and police attendances; levels of absenteeism, exclusion and criminality; and teaching assistant and other help in school.

Resource use data is collected to enable an economic evaluation alongside a clinical trial. Evaluation will include health-related quality of life assessment, with utility measures based on the CHU-9D, the cost of consultations, medications, remedies, supplements and room hire, to enable QALY and ICER calculation. The time horizon is 1 year, during which time resource use will be collected from therapists, who complete therapist forms at each consultation documenting the time spent, the venue, medications or supplements given.

#### Feasibility outcomes (Table 2)

Key feasibility criteria are the ability to recruit a cohort and to recruit to the interventions within the stated time frame of 2 years, by measuring recruitment rates and time taken. Numbers recruited in 2 years will be extrapolated to estimate the time needed to recruit to a full trial, and longer than 4 years will not be considered feasible. The feasibility of recruiting a representative cohort will document ADHD severity, number and type of co-morbidities, medications taken, resource usage, levels of exclusion, and criminality, and recruiting from nationally funded ADHD facilities such as special schools, secure units, NHS facilities and support services.

**Table 2 Tab2:** Feasibility criteria

Criteria	Measurement	Criteria for continuation to a full trial
Recruitment to cohort rates	Number recruited in 2 years	% recruited/sample size estimation. Minimum acceptable to proceed to a full-scale trial will consider the number of years needed to recruit the required sample size. Numbers recruited in 2 years will be extrapolated to determine how long a full trial would need to be. The required sample size will be divided by the percentage recruited in 2 years. Duration of the full trial of more than 4 years will not be considered feasible.
Recruitment to treatment rates	Percentage accepting offer	At least 30%. The percentage of participants refusing treatment will be considered to determine acceptable levels of refusal. Too many treatment refusers may lead to a high chance of a type II error and inadequate information to estimate critical parameters for a full trial with reasonable precision.
Treatment effects (statistical significance)	Standard mean difference (SMD) CGI	Mean = < .3. Since neither intervention has been tested in this form previously, estimation of the effect size cannot consider previous estimates. Since we need to know that therapies show some evidence of being helpful, a SMD of 0.3 in those implementing the therapies will be considered sufficient to proceed to full trial.
Treatment effects (clinical significance)	CGI *T* score	5 percentiles. A *T* score change of 5 percentiles is considered clinically significant, since the child has moved from one level of severity to another according to Conners (2009) [47].
Attrition: cohort	Number of PQs returned at 6 months	At least 30%
Attrition: consultations	Number of consultations attended	Adjustment of intervention provision
Acceptability of TQ and CQ	Number of TQs and CQs completed at baseline and 6 months; number of email/telephone/ paper responses	Adjustment of measure, collection methods and trial parameters. Questions reworded or removed dependent on discussion with carers and teachers, and optimum means of delivering questionnaires explored
Adverse events	Clinicians records	No severe adverse events as defined by the Common Terminology Criteria for Adverse Events guidelines
Appropriate outcome measurement	Number of missing items	Adjustment of measure
Recruitment of therapists	Number recruited fulfilling criteria	At least two for each therapy
Statistical analysis	ANCOVA	Meets assumptions

Whether suitable homoeopaths and nutritional therapists can be recruited will be assessed, with recruitment of two therapists for each intervention considered the minimum required. The uptake of treatment will measure the number of appointments kept and missed; the taking of homoeopathic medicines; and the implementation of advice, diets, and the taking of supplements. At least 30% will need to have accessed treatment, and at least 70% of those to have attended at least three consultations, to continue to the full trial. It is anticipated that there may be high dropout rate and chaotic uptake. The percentage of participants refusing treatment will be considered to determine acceptable levels of refusal since too many refusers may lead to high chance of a type II error and inadequate information to estimate critical parameters for a full trial with reasonable precision.

Adverse events will be documented to measure the safety of the interventions using the Common Terminology Criteria for Adverse Events (CTCAE, 2010). Any severe adverse events as a result of treatment will mean the intervention will not continue to full trial.

The acceptability of the outcome measurements will assess rates of completion by parents and teachers at each time point in the study. Collection methods will be adjusted if necessary. Their suitability will also be assessed by ascertaining whether information can be accurately and usefully collected about ADHD symptoms, health-related quality of life, criminality, school exclusion, attendance, extra help, professional resource use, medication and other intervention use and adjusted as necessary. Whether CGI and SNAP are appropriate and sensitive enough to measure therapist- and participant-perceived change will be assessed and measures adjusted accordingly. The measure will be adjusted if any systematically missing items are identified. The suitability and appropriateness of statistical analyses to interpret results will also be assessed.

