## Methods

### Recruitment

At least 140 children aged 5–18 with a diagnosis of ADHD and any accompanying co-morbidities are recruited to an observational cohort and their consent to participate in the cohort is sought by completion of a questionnaire with embedded consent to be contacted again. Their outcomes of interest are measured at recruitment (baseline) and every 6 months, via these questionnaires, which are completed by carers and blinded teachers. Carers of children with ADHD were involved in the selection of items for, design and pilot testing of the questionnaire, advised about recruitment and sat on the steering committee.

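### The recruitment go/no-go formula in Table 2 does not give a time; computed as intended, the minimum of 140 children in 2 years projects to 7.1 years in the plan's own worked example, against a 4-year limit

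*Protocol article*

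**What the plan says.** In the protocol article, Feasibility outcomes, the ability to recruit the cohort "within the stated time frame of 2 years" is a key criterion. The number reached is to be projected forward to the time a full trial would need, and "longer than 4 years will not be considered feasible". The Table 2 row on cohort recruitment repeats this aim and the limit, and gives the calculation: "The required sample size will be divided by the percentage recruited in 2 years". The same row describes the percentage as the number recruited relative to the estimated sample size.

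The figures that feed the rule stand elsewhere. The Recruitment section sets the cohort at "At least 140 children aged 5–18 with a diagnosis of ADHD". The Sample size section gives a worked full trial: "If an effect size of .4 is obtained in the pilot, then the outcomes of approximately 100 participants per group will be required". With attrition of 40%, "then 166 participants per group will need to be recruited to the cohort". The Randomisation section describes three arms, and the Discussion says that a full trial would test the same two interventions.

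**The concern.** The rule has a threshold in years, but its printed formula does not return years. Someone applying it after the pilot would have to choose an interpretation with the recruitment figure already known, which is what a pre-stated continuation criterion should prevent. The Discussion makes progression to a full trial depend on the feasibility criteria being met, and recruitment is the first of them.

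Once the formula is put right, a second point appears. The plan prints a cohort minimum, a worked full-trial size and a time limit, but never sets them side by side. A reader could assume that reaching 140 in 2 years satisfies the recruitment criterion. In the plan's own example it does not. The article also leaves open whether children recruited in this internal pilot count towards the full-trial N, and whether the 4 years include the 2 pilot years. These choices change the pass mark considerably.

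**Working it through.** **Inputs**
- Cohort minimum: 140 (Recruitment). Window: 2 years (Feasibility outcomes). Joining the two gives 140/2 = 70 per year.
- Worked full trial: SMD 0.4, alpha 0.05, power 80%, about 100 analysed per group, 40% attrition, 166 recruited per group (Sample size).
- Groups: three, two interventions plus usual care, taken as equal in size because the plan gives its figure per group.
- Limit: 4 years.

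**Reproducing the plan's sample size**
- Two-sample comparison of means, SMD 0.4, two-sided 5% (the pilot tests are two-tailed; assumed the same here), 80% power: 99 per group. The plan says approximately 100.
- Allowing for attrition: 100/(1 − 0.40) = 166.7. The plan says 166.
- Total: 3 × 166 = 498. This total is not printed in the article; it follows from the figures above.

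**The formula as printed**
- Percentage of the required sample recruited: 140/498 = 28.1%.
- Treated as a fraction: 498/0.281 = about 1,772.
- Treated as a percentage number: 498/28.1 = 17.7.
- Neither is a number of years, since the 2-year window appears nowhere in the division.

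**The formula as intended**
- Projected years = 2 × required N / number recruited in 2 years. Equivalently, 2 years / fraction of required N recruited.
- 2 × 498/140 = 7.1 years. Check: 2/0.281 = 7.1.
- Crediting the 140 pilot children: (498 − 140)/70 = 358/70 = 5.1 further years.

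**Implied pass mark at N = 498, with R the number recruited in 2 years**
- All 498 within 4 years: 2 × 498/R ≤ 4, so R ≥ 249.
- Pilot children credited and 4 further years allowed: 2 × (498 − R)/R ≤ 4, so 498 ≤ 3R and R ≥ 166. That this equals the per-group figure is a coincidence of dividing 498 by 3.

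**Sensitivity at 70 per year**
- The two 20% losses compounded instead of added: 100/0.64 = 156.25, so 157 per group and 471 in total. That is 471/70 = 6.7 years, or (471 − 140)/70 = 4.7 further years with crediting.
- 20% attrition only: 300/0.8 = 375. That is 375/70 = 5.4 years, or (375 − 140)/70 = 3.4 further years with crediting, which passes.
- With crediting and 4 further years, 140 + 280 = 420 children are available. Three groups of 100 analysed then fit if the loss is at most 1 − 300/420, about 28%.

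**The case against.** The strongest reply is that this is one badly worded sentence and not a missing rule. The text says that numbers will be extrapolated and compared with 4 years, and the table row supplies the ratio that is needed; replacing the required sample size by 2 years as the dividend gives 7.1 at once. That is right, and it is why the remedy is a correction of wording. It does not make the printed formula usable.

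The second reply is that failing the limit at 140 is no contradiction. The figure is a floor, and the Sample size section ties the pilot's size to at least 30 per arm so that the standard deviation can be estimated. A continuation mark stricter than that floor is legitimate. The worked full trial is also conditional on an SMD of 0.4 and 40% attrition. This stands.

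Three stronger readings are therefore tempting but unsupported:
- A reader might infer that the criterion gives a wrong answer fixed in advance. If recruitment really is 70 per year and 498 are needed, a finding of more than 4 years is correct under the stated limit. The outcome is not fixed either, because N will be recalculated from the observed effect and attrition.
- A reader might infer a conflict with the criterion of an SMD of 0.3. The feasibility criteria apply jointly, so passing one and failing another is not a conflict. The 0.3 also refers to those who implement the therapies, not to everyone offered them.
- A reader might infer that on-target recruitment passes only if the pilot SMD is about 0.53 or more. That uses 280 children in 4 years (280/3 × 0.6 = 56 analysed per group) and no crediting. With the 140 credited and 4 further years, 420/3 × 0.6 = 84 are analysed per group, and the threshold falls to about 0.43.

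**Conclusion.** The printed formula is wrong as a decision rule, because it cannot produce the number of years that the limit requires. The intended rule is clear from its context and simple to state.

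Under that rule and the plan's illustrative figures, recruiting exactly the minimum of 140 in 2 years gives 7.1 years in total or 5.1 further years, so the 4-year limit is missed on either count. This rests on three equal groups, a constant rate of 70 per year, the additive 40% loss and an SMD of 0.4, and it counts recruitment time only. A lower loss combined with crediting of the pilot children could bring the projection under 4 further years, so the unresolved crediting question can decide the result. No effect estimate or participant-level analysis depends on this sentence; the go/no-go decision on recruitment does.

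**What to change.** In the Table 2 row on cohort recruitment, replace the division sentence with: projected years = 2 × required N / number recruited in 2 years. Then add:
- whether children recruited in the internal pilot count towards the required N;
- whether the 4 years include the 2-year pilot period;
- the implied pass mark for the worked example (N = 498): at least 249 in 2 years if the whole sample must be recruited within 4 years, or at least 166 in 2 years if pilot children are credited and 4 further years are allowed;
- a plain statement that reaching 140 would not by itself meet the recruitment criterion in this example, and that the final N will depend on the pilot's effect size and attrition.

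The 4-year limit should not be moved to make a pilot of 140 pass, because that would tune a stopping criterion to the planned enrolment. The cost is a corrected sentence and a few added lines, with no extra participants and no change to any analysis. The stated outlook for recruitment becomes less favourable.
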